# 2. the proposed trial

**2.1 Study Design:**This is a Type 1 Effectiveness-Implementation Hybrid Design2 1:1 parallel single (assessor)-blinded randomized controlled trial (RCT) conducted online with participants from four Canadian sites (B.C.; London, ON; and two in Toronto, ON) to evaluate the 6-week effectiveness (and the 4-week retention effect) of SMART on patient-relevant outcomes, while documenting implementation factors.59Following the [RE-AIM](http://www.re-aim.org/) framework, a planning tool for implementation evaluation,60 we will assess the implementation of SMART. Also, a small end-of-trial qualitative study will be used to understand participants’ experience.61

**2.2 Trial Interventions:** Participants allocated to the intervention group will receive usual care after the LLA and access to **SMART**. We provide a detailed description of SMART using the TIDieR (Template for Intervention description and Replication) checklist62 provided in **Appendix B**. In **Appendix C** we provide a list of BCTs adopted for each module according to our systematic review and meta-analysis.41 Participants will access the SMART platform using their own computer/tablet, and will be screened for having a computer/tablet before enrolling in the study. In rare cases where a participant in B.C. does have a tablet, they may receive a tablet (Apple’s iPad) preloaded with a dedicated icon to enable direct connection with the SMART platform, if needed. Tablets will not be able to be provided to participants in Ontario.

**Content:** SMART is web-based eHealth intervention that has six educational and skill development modules. SMART is accessible through this link: <https://360.articulate.com/review/content/1afbca12-f6bb-465e-b40f-1029a6fa981b/review>

We will ask participants to complete one module each week, at their own convenience, over the 6-week intervention period. Module 1 overviews the SMART program as well as ‘self-regulatory skills,’ which are key for turning intentions into behavior (e.g., goal setting, rating confidence). Other modules include managing mental health wellness (managing depression and distress, body image and sexual health), physical health (skin of the sound limb, diet and weight control, pain management, falls prevention and management), residual limb management (skin care, positioning and shaping of residual limb), managing a prosthesis (wearing a liner, sock management), and managing daily living activities (transferring to bath tub, driving). The modules are 20-30 minutes in duration and consist of goal setting, instructional videos of peers, and narrative power point presentations. Each module starts with an overview, includes evaluation of the previous module’s goals, and ends with goal setting. There is also a resources icon which provides more information and resources based on the questions and issues most-frequently raised in our focus groups, such as journey and timeline after LLA, and funding support for prostheses.

**Delivery:** SMART will be delivered with the support of peers using Brief Action Planning (BAP) tool,63 based on motivational interviewing64 which assists with goals setting and action planning and can enhance self-efficacy with self-management. Six peer facilitators identified by our clinician partners will be recruited in BC and ON. Peers are mentors with LLA who support, act as role models,65 and facilitate motivation using/establishing goal setting and action planning. Peers will take the online BAP training ([Centre for Collaboration, Motivation and Innovation](https://ccmi.learnupon.com/store/300131-brief-action-planning-certification)) [**Appendix D**].63 Peer facilitators will be assigned to each study site (BC and ON), and will provide a 20-minute weekly telephone call or Zoom video call, hosted by the University of British Columbia, to the SMART group participants, for 6 weeks.63 This call will help the participant set their goals, promote BAP, evaluate weekly progress, and provide support. All participants in the SMART group will receive online training on the online SMART platform from the trainer, who will be a researcher with clinical background with more than 10 years clinical and research experience with people with LLL. In British Columbia, participants will also be recruited from sites in the different health authorities: Fraser Health (Abbotsford Regional Hospital and Cancer Centre, Chilliwack General Hospital, Peace Arch Hospital, Ridge Meadows Hospital, Surrey Memorial Hospital, and Queens Park Health Care Centre), Interior Health (Kelowna General Hospital), Northern Health (Prince George Hospital), and Vancouver Island Health Authority (Victoria General Hospital, and Nanaimo Regional General Hospital). The trainer will arrange the first online meeting with the peer facilitator. The SMART platform will be asynchronously monitored through a web portal by the trainer, who observes participant progress and provides feedback if required. If there is no online activity within a 7-day (consecutive) period, the trainer will contact the participant to inquire about the reasons for inactivity and troubleshoot any problems.

**Control Intervention:**Participants in the control arm will receive usual care after LLA, education, and social calls. The education booklet is typically offered to patients at discharge, and includes information about LLA consequences, adjusting to amputation, pain management, limb positioning and exercises, mobility (e.g., wheelchair safety, hopping, and transfers), residual limb management (e.g., skin care and diabetic foot care), tips for preparing the home, and driving. A single weekly structured email or telephone contact (based on preferences, n=6 in total) will be made by the trainer. The purpose of the contact is to answer any questions, and to help control for attention bias.45

**2.3 Allocation - Sequence Generation and Randomization:**We will use a central computerized randomization process with variable block sizes to randomly allocate the participants to the intervention (SMART) group or control group using a 1:1 ratio by an independent statistician.

An independent statistician will provide the randomization list through REDCap (REDCap Software, Vanderbilt University and National Institute of Health, USA). The research coordinator will obtain written informed consent (Over Qualtrics platform) and a blinded assessor will complete the baseline assessment. The research coordinator will meet with the participant over Zoom (a secure, UBC-based platform) to guide them through the consent form and answer any questions. At the completion of baseline assessment, the research coordinator will log onto the system to determine the next allocation. The research coordinator will work with the group trainers to set up an appointment. Our protocol for all participants is to complete the baseline assessment, randomization and training within two weeks.

**2.4 Protecting against bias - Blinding:**Blinding of participants for the RCTs on the effect of eHealth interventions is impossible because of nature of intervetnions.66 Therefore, it is difficult to blind participants to the intervention received. The assessors will be blinded to group allocation, we will complete the primary outcome (TUG and ASCQ) first, and participants will be asked not to disclose their group allocation during assessments.66 Furthermore, we will have separate trainers for each group (to minimize trainer bias); and the primary outcome measure, the TUG is a performance-based measure with standardized instructions. Finally, all statistical analyses will be conducted by a blinded statistician.

**2.5 Inclusion and Exclusion Criteria:**To be included, participants will: have a unilateral dysvascular- or diabetic- related LLA (transtibial or transfemoral);3have conducted the casting for their initial prosthetic limb (up to 2 years); be aged ≥ 50 years (85% of adults with LLA);3 have a computer or tablet and have access to the internet, and self-identify as being able to speak and read English. We will exclude adults with substantial health conditions (e.g., congestive heart failure, diagnosed dementia); those anticipating further surgery (e.g. LLA revision) as identified by our study sites’ physiatrists; and an ability to use a tablet (e.g./ using hands for typing). Given these criteria, the results of this study will not be generalizable to all adults with LLA such as the very young and those who do not speak English. As most people with LLA are >50 years old and more than 90% of the population of BC and ON speak English, we are confident of obtaining a representative sample.

**2.6 Duration of Intervention:**Participants in the SMART group will receive the intervention for six weeks. Participants in the control group will be contacted weekly for a similar 6 week period.

**2.7** **Frequency and Duration of Follow-up:**There are six weekly SMART modules with each taking approximately 20 to 30 minutes to complete. Individuals will be encouraged to complete one module a week to reduce any perceived burden, and gradually integrate the information. Participants from both groups will receive a weekly contact: SMART group participants will receive a 20 minute telephone call/Zoom video call from peers, and the Control group participants one email or phone call by trainer.

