**2.15 Study Centers:**We will recruit 82 individuals, equating to 20 or 21 participants per site. Multiple sites were chosen to understand the diversity of LLA population and health services: In British Columbia, we will recruit from GF Strong and Holy Family Hospital in Vancouver, BC, where approximately 100 adults with new LLA receive care each year. Participants will also be recruited from hospitals in 4 additional British Columbia Health Authorities: Fraser Health, Interior Health, Northern Health, and Vancouver Island Health; Sunnybrook and West Park in Toronto, each with over 100 inpatients per year; and Parkwood Hospital in London, ON, where more than 75 older adults with new LLA receive care. Our community partner Barber Prosthetics ([name] and [name]) will assist with recruitment through their extensive network in Metro Vancouver (Burnaby to Hope).

[figure not shown]

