| Who provided | The trainer will spend less than 2 hours to provide instruction for a participant to learn how to use the SMART, at baseline (T1). The SMART platform will be asynchronously monitored through a web portal by the trainer, who will observe participant progress and provide feedback if required. If there is no online activity within a 7-day (consecutive) period, the trainer will contact the participant to inquire the reasons for inactivity and troubleshoot any problems including technical issues.  Two peers will be identified by our clinician partners at each study site. Peers are mentors with LLA who support the individuals with LLA.65 The assessor will be a trained research assistant who will be blinded to participants assigned groups. The assessor will evaluate all participants at baseline (T1), end of the intervention (6-weeks) (T2), and 4-week retention period (T3). |
| How (modes of delivery) | SMART is an online, educational and training platform for individuals with LLA that is asynchronously monitored by a trainer through a website. SMART will be delivered via computer or tablet with support of peers. |
| Where | Participants will use one module of SMART per week. All participants will be evaluated by an assessor online via Zoom (a secure, UBC-based platform) at T1, T2, and T3. |

**Appendix C:** Behavioural change techniques used for contents of modules in Self-Management for Amputee Rehabilitation Using Technology (SMART)

| **BCTs** | **Self-regulatory skills** | **Mental wellness** | **Physical health** | **Residual limb management** | **Managing a prosthesis** | **Managing daily living activities** |
| --- | --- | --- | --- | --- | --- | --- |
| Goal setting (behaviour) | * | * | * | * | * | * |
| Problem solving |  | * | * | * | * | * |
| Action planning |  | * | * | * | * | * |
| Self-monitoring of behaviour |  |  | * | * | * | * |
| Social support (practical) | * | * | * | * | * | * |
| Social support (emotional) |  | * | * | * | * | * |
| Instruction on how to perform a behaviour | * | * | * | * | * | * |
| Information about antecedents |  | * | * | * | * | * |
| Information about health consequences |  | * | * | * |  |  |
| Demonstration of the behaviour |  |  | * | * | * | * |

**Appendix D.** Brief Action Planning (BAP) Flowchart

Developed by Steven Cole, Damara Gutnick, Connie Davis, Kathy Reims

Accessed from: <https://centrecmi.ca/wp-content/uploads/2018/11/BAP_flow_Chart_2016-08-08.pdf>

[figure not shown]

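### Recruiting site enters neither the stated randomisation nor the stated ANCOVA in a four-site trial of about 20 participants per site, at some cost in precision and credibility

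*Protocol*

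**What the plan says.** Section 2.1 describes a trial conducted online with participants from "four Canadian sites (B.C.; London, ON; and two in Toronto, ON". Section 2.15 sets the total at 82, or 20 or 21 per site, and gives the reason for using several sites: "Multiple sites were chosen to understand the diversity of LLA population and health services".

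Section 2.3 describes allocation as a "central computerized randomization process with variable block sizes", 1:1, and adds: "An independent statistician will provide the randomization list through REDCap". The research coordinator logs on after the baseline assessment to obtain the next allocation. No stratification factor is named. The protocol's only mention of stratification, in section 2.10, concerns a later implementation study.

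Section 2.16 compares all primary and secondary outcomes by ANCOVA, adjusted for the baseline score and for inpatient and outpatient units. Site is not among the covariates.

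**The concern.** Blocks that run across sites keep the trial total near 41:41 but do not control the split within a site. With about 20 people per site, a lopsided site is quite likely. The protocol chose its sites because their populations and health services differ, so it is plausible that site predicts outcome. If it does, an uneven split by site adds noise to the treatment comparison, and the stated model has no term to remove it. A reader of the results could also fairly question an arm drawn largely from one site. The stakes are precision and credibility in a trial sized for 80% power with little to spare.

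**Working it through.** **Inputs from the protocol.** 82 recruited, four sites, 20 or 21 per site, 1:1 allocation (sections 2.1, 2.3, 2.15). Difference 13.6 m, SD 19.9 m, two-sided 5% level, 80% power, 34 per group at final assessment (section 2.10).

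**Assumptions.** Block sizes are not stated; sets of 2/4, 4/6 and 4/6/8 were tried and gave nearly the same results. Sites are taken as 21, 21, 20 and 20, with random order of arrival. The share of outcome variance due to site (ICC) is not given; 0.01 to 0.20 is used. The metre figures use the two-minute walk test because section 2.10 gives an SD only for that measure; none is given for the TUG or ASCQ, which sections 2.4 and 2.8 treat as primary.

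**1. The plan's own figure.** n per group = 2 × (1.96 + 0.8416)² × 19.9² / 13.6² = 33.6, rounded up to 34. It reproduces. The SE of the difference is then 19.9 × √(2/34) = 4.83 m.

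**2. Imbalance within a site.** With 41:41 overall, the SMART count at one site is close to hypergeometric:
- site of 20, 14 or more in one arm: 7.0%
- site of 21, 14 or more in one arm: 12.8%
- average over the four sites: (2 × 7.0% + 2 × 12.8%) / 4 = 9.9%, about 0.10 per site.

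Simulation with blocks of 4/6/8 gives a probability of about 0.31 that at least one of the four sites has 14 or more in one arm. A within-site difference of 8 or more (such as 14:6) occurs in some site with probability 0.19. With site-stratified blocks, no simulated trial had a difference of 6 or more at any site.

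**3. Effect on the estimate.** Let w be the share of the SMART arm from a site minus the share of the control arm from that site. The chance shift has mean zero and variance ICC × 19.9² × Σw². In simulation Σw² averages 0.0371 at 82 participants, which scales to 0.0371 × 82/68 = 0.0447 at 68. For stratified blocks of 4/6 it is 0.0018 at 82, scaled in the same way.

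| Assumed site ICC | SD of shift, central list | SD of shift, stratified list |
| --- | --- | --- |
| 0.01 | 0.4 m | 0.1 m |
| 0.05 | 0.9 m | 0.2 m |
| 0.10 | 1.3 m | 0.3 m |
| 0.20 | 1.9 m | 0.4 m |

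**4. Power of a site-adjusted analysis.** With 17 per site at final assessment, and taking the residual SD as still 19.9 m (no gain from adjustment), the information retained relative to perfect balance is:
- central list: 0.955 on average, so 34 × 0.955 = 32.5 per arm, power 78.6%
- central list, 5th percentile of balance: 0.886, so 30.1 per arm, power 75.6%
- stratified list: 0.996, so 33.9 per arm, power 80.3%.

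**5. When adjustment pays on a central list.** Per unit of outcome variance, the unadjusted variance is (1 − ICC) × 2/34 + ICC × 0.0447, and the adjusted variance is (1 − ICC) × (2/34) / 0.955. They are equal at an ICC of about 0.06. Below that, adjustment costs a little; above it, adjustment gains. At an ICC of 0.20 the SEs are 4.71 m unadjusted and 4.42 m adjusted, and 4.33 m adjusted with a stratified list.

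**The case against.** The strongest reply is that randomisation already protects the comparison. The estimate is unbiased over repeated allocations, and even at an ICC of 0.20 the chance shift is small against 13.6 m. That stands. A reader might infer that site effects are confounded with treatment; the documents do not support that, because the imbalance is random and not systematic.

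A reader might also infer that usual care and devices are tied to site. No section says that usual care is fixed by site; section 2.15 speaks only of diversity. Participants use their own device, and loan tablets are a rare exception in B.C.; the statement that "Tablets will not be able to be provided to participants in Ontario" concerns that exception. Peer calls are by telephone or Zoom and assessments are by Zoom, so the sites act largely as recruitment sources. The unit covariate in section 2.16 already captures part of the care setting. All this makes large site effects less likely but does not exclude them.

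Section 2.2 says "Peer facilitators will be assigned to each study site (BC and ON"), which may suggest that stratifying would also deal with differences between peers. It would not. Peers serve only the SMART arm, so their effects enter the contrast however well sites are balanced. How many peers there are is likewise a separate matter.

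Finally, the protocol is silent on stratification and does not rule it out; the REDCap list or an analysis plan not shown may deal with site. That also stands. However, the protocol does describe the allocation and does list the ANCOVA covariates, and site is absent from both.

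**Conclusion.** The point holds as a matter of precision and credibility. As written, neither the allocation nor the model accounts for site, and the chance that at least one site has 14 or more participants in one arm is about 0.31. The consequence is modest: a zero-mean shift with an SD of about 0.4 to 1.9 m, no bias and no change to the 34 per group. Stratifying raises the power of a site-adjusted analysis from about 78.6% to about 80.3%. These figures rest on assumed block sizes, equal recruitment by site, a site ICC of 0.01 to 0.20 and the two-minute walk test SD. Whether site predicts outcome in this population cannot be learned from the protocol.

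**What to change.** In section 2.3, state that the REDCap list is stratified by recruiting site (B.C.; London; each of the two Toronto sites), with variable block sizes concealed from the coordinator and sites. In section 2.16, add site as a covariate in the ANCOVA beside baseline score and unit. If the list is already stratified, say so and make the model match. If enrolment has begun, keep the existing list and add site to the model before any unblinded look at the data, accepting a small loss of precision if the site ICC turns out below about 0.06.

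The cost is a new list upload and 3 model degrees of freedom, with no extra participants. Incomplete final blocks can leave the overall split uneven: across the block sets simulated, the largest overall arm difference was 6 to 10, against 2 to 4 with the central list. Allocation also becomes somewhat easier to guess within strata of about 20, and the coordinator sees each assignment, so block sizes must stay concealed. B.C. as one stratum still pools several health authorities, so differences within the province remain uncontrolled.
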